To test the primary outcome measure hypothesis that the EMADE physiotherapy intervention, as described will perform better than usual care, the difference in group means of the primary outcome, OMAS values at 12 weeks post surgery, will be statistically compared. This will be through applying an independent *t* test with significance taken as *p* value of ≤ 0.05 and the inclusion of confidence intervals (CI at 95% CI and *p* value of ≤ 0.05 threshold). Where data is not found to be normally distributed such that parametric tests cannot be utilised, the non-parametric Mann-Whitney *U* test will be employed (*p* value ≤ 0.05).

There is a lack of consensus in the academic literature on how to handle missing data [35, 36]. However, based on the 120 sample size, the following sequential approach will be applied for the primary outcome:If missing data is 5% or less, conduct analysis based on complete-case analysisIf missing data is greater than 5% and up to 10%:Conduct analysis based on pairwise deletion (assuming missing at random (MAR)) and thenConduct multiple imputation analysisIf these two analyses yield comparable results, then it will be assumed that the missing data has not influenced the outcome of the trialIf the two analyses yield notable differences, to accommodate for the missing data, sensitivity analysis will be conducted based on the statistician’s adviceIf missing data exceeds 10%, detailed discussions will be held with the study statistician

Interpretation of secondary outcome and sub-group analysis will require caution due to risks of type II errors and, because of where post hoc analysis may demonstrate association, causation may not be supported. Secondary analyses will be performed for hypothesis generation. The difference in group mean scores for the secondary outcomes; EQ-5D-5 L and A-FORM at 12 weeks post surgery will be analysed in a similar manner to the primary outcome. The one-way analysis of covariance (ANCOVA), including follow-up time as a covariance, will be applied to assess these outcomes across the complete study period.

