Adjustment for baseline scores, through analysis of covariance, will be conducted for OMAS, EQ-5D-5 L and A-FORM and compared with unadjusted scores. Impact of covariates will be further explored through regression analysis. Initial analysis for co-variates where significance is nearly reached (*p* > 0.10) will be taken forward into a statistical model. Due to the bimodal impact of age and sex, these will be included in this analysis. Other exploratory analysis for potential covariates may include impact of smoking, previous level of physical activity, type of fracture (AO classification), complexity of surgical repair and any subsequent removal of metal work; most notably removal of syndesmosis screw(s) for which stratification was applied at randomisation. Analysis will also be conducted using modified ITT by excluding those participants who attend only one session or less of EMADE sessions.

Sub-groups will include return to work for those unable to work due to their ankle fracture at the time of randomisation, and similarly, return to driving for those unable to drive due to their ankle fracture at the time of randomisation. Frequency of complications will be described but, based on the published literature, it is anticipated that frequency will be sufficiently low not to warrant statistical analysis.

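### The covariate screen is printed with its inequality reversed: p > 0.10 contradicts the sentence's own words and would favour unrelated covariates in an exploratory regression

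*Protocol article*

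**What the plan says.** All the relevant text is in the Data processing section of the protocol article.

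- **The screen:** "Initial analysis for co-variates where significance is nearly reached", with p > 0.10 given in brackets as the condition, "will be taken forward into a statistical model".
- **Age and sex:** "Due to the bimodal impact of age and sex, these will be included in this analysis".
- **Baseline scores,** handled apart from the screen: "Adjustment for baseline scores, through analysis of covariance, will be conducted for OMAS, EQ-5D-5 L and A-FORM and compared with unadjusted scores".
- **Further candidates:** after the screening sentence, the article lists smoking, earlier physical activity, AO fracture class, complexity of the repair and later metalwork removal. It presents these as other exploratory work that may be done.
- **Primary analysis** of 12-week OMAS: "This will be through applying an independent *t* test", "with significance taken as *p* value of ≤ 0.05", with a Mann-Whitney fallback. No covariate enters.

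The section introduces the covariate regression as further exploration and describes the secondary analyses as hypothesis-generating.

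**The concern.** The sentence gives its selection rule twice, once in words and once in symbols, and the two disagree. A covariate that has nearly reached significance has a small p-value. The condition p > 0.10 picks out those that have not come near it.

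The rule cannot be carried out as written without choosing between words and symbol, and at least three readings are open:

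- p > 0.10, the literal symbol;
- p < 0.10, the usual liberal screen;
- p between 0.05 and 0.10, taking the words strictly.

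Each gives a different model, and the choice would be made when the outcome data are already in hand. If the symbol were followed, the stronger a screened covariate's relation to outcome, the less likely it would be to enter a regression meant to explore covariate impact.

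**Working it through.** **Step 1. Is the sign corrected elsewhere?** No. Every other significance threshold in the Data processing section is p ≤ 0.05, so small values count as significant throughout. The screening rule appears once only. Other inequality signs in the same section are intact, so there is no sign that the symbol was damaged in text extraction.

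**Step 2. Sample size for the check.** The Sample size calculations section gives a difference of 10, SD 19.5, 5% significance, 80% power and 120 in total. Two-sided testing is assumed, since sidedness is not stated.

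n per arm = 2 × (1.960 + 0.842)² × 19.5² / 10² = 2 × 7.849 × 3.8025 = 59.7, rounded up to 60, so 120 in total. The plan's figure is reproduced, and power at 60 per arm is 80.2%. A noncentral-t calculation gives 61 per arm (122), which is close enough. N = 120 is used below.

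**Step 3. How often the screen keeps a covariate.** Assumptions, none of them in the article: one continuous covariate is tested at a time, with a two-sided p-value, and its true correlation with outcome is r. The article says only that there is an initial analysis and gives no correlations, so a range is shown. Each row comes from 20,000 simulated trials.

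| Assumed r | Kept if p > 0.10 (as printed) | Kept if p < 0.10 |
|---|---|---|
| 0 (unrelated) | 90.0% | 10.0% |
| 0.1 | 71.1% | 28.9% |
| 0.2 | 28.7% | 71.3% |
| 0.3 | 4.4% | 95.6% |
| 0.4 | 0.1% | 99.9% |
| 0.5 | about 0% | about 100% |

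**Step 4. Check by formula.** By Fisher's transformation the test statistic is roughly normal with mean m = atanh(r) × √(N − 3) and variance 1, so P(p > 0.10) ≈ Φ(1.645 − m) − Φ(−1.645 − m). With √117 = 10.817:

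- r = 0.1: m = 0.1003 × 10.817 = 1.085; Φ(0.560) − Φ(−2.730) = 0.712 − 0.003 = 0.709.
- r = 0.2: m = 0.2027 × 10.817 = 2.193; Φ(−0.548) − Φ(−3.838) ≈ 0.292.
- r = 0.3: m = 0.3095 × 10.817 = 3.348; Φ(−1.703) ≈ 0.044.

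These agree with the simulation. The two right-hand columns of the table sum to 100% because one rule is the complement of the other. The 90% for unrelated covariates follows directly from the definition of a p-value and needs no assumed correlation.

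**Step 5. The strict in-between reading.** Keeping only p between 0.05 and 0.10 retains 4.9%, 10.0%, 11.7% and 3.9% of covariates at r = 0, 0.1, 0.2 and 0.3. The three readings therefore lead to materially different models.

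**The case against.** The best defence is that this is a slip of one character. The words show the intent, small p means significant everywhere else in the section, and a competent analyst would follow the words. Even under the literal rule, the initial analysis would still show which covariates are associated with outcome. It is indeed probable that p < 0.10 was meant. But a decision rule in a protocol should not need reinterpreting at the analysis stage, and the words do not settle whether p < 0.10 or the strict in-between band was intended.

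The defence is right to limit the reach of the error. A reader might infer three stronger things that the article does not support.

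- **That the trial's main result is at risk.** The primary comparison is an unadjusted t test and does not use the screen. Neither does the sample size.
- **That the adjusted analyses lose all the prognostic covariates.** Age and sex are included in any case, and baseline OMAS, EQ-5D-5 L and A-FORM are adjusted for in an analysis of covariance that is not screened.
- **That smoking, physical activity and AO class would be discarded.** They are listed after the screening sentence as other exploratory work that may be done. It is plausible that they pass through the screen, but the article does not clearly say so.

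A preference for a fixed covariate list over p-value screening is a separate modelling view about an exploratory analysis. The final list may also properly sit in an analysis plan that is not shown. It is not part of the error.

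**Conclusion.** The point holds as an error in a stated rule: the inequality contradicts the sentence's own words and the section's significance convention, and no other text corrects it. Taken literally at N = 120, the screen keeps about nine in ten unrelated covariates, and about 71%, 29% and 4% of those with correlations of 0.1, 0.2 and 0.3. The last three figures rest on assumed correlations, testing one covariate at a time, and 120 analysed participants. The direction of the reversal depends on none of these.

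Severity is modest. The damage is confined to an exploratory regression and to whichever covariates are put through the screen. No effect on the treatment estimate or its confidence interval has been quantified, and none is claimed.

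**What to change.** Change the threshold in the screening sentence to p < 0.10 (or p ≤ 0.10), and state in the same place that age and sex enter the model whatever their p-value. It would help to say at the same time which of the listed candidates go through the screen.

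Optionally, name the covariates in advance and drop the screen. That would be a refinement and is not needed to correct the error.

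The cost is one character and a short clause. No new data are needed, and the sample size and primary analysis do not change. The article expects the last recruit in mid 2018 and follows participants to 52 weeks, so on its own dates the correction can be made before the final analysis.

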### Participant timeline

Recruitment and consent may take place from the in-patient stay until and including the 2-week post-surgery outpatient review. Only after all baseline outcome measures are recorded, does randomisation take place, see Figs. 1 and 2.

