**Fig. 2 Fig2:**
[figure not shown]
A schematic diagram of the patient’s journey through the early motion and directed exercises (EMADE) ankle study. Key: *EMADE* early motion and directed exercise, *PROMs* patient-reported outcome measures

The data collection time points (post surgery) are: baseline at 2 weeks, end of intervention at 6 weeks, and at three research follow-up time points; 12 weeks and 24 weeks as short- and mid-term follow-ups, respectively, and at 52 weeks as a long-term follow-up and the trial end point. For participant’s convenience, the 2-week and 6-week EMADE sessions are combined with the orthopaedic 2-week and 6-week reviews. The 12-week, 24-week and 52-week PROMs data may be collected via either return post (postage pre-paid), electronically or in person according to participant choice. Participants undergoing objective assessment will attend the David Greenfield Human Physiology Unit, Medical School, University of Nottingham, UK.

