### Allocation and Blinding

An online computer service, www.sealedenvelope.com is used for randomisation. This facility generated the codes concealed from the research team, on a 1:1 allocation basis to either group, with random order of permuted blocks (sizes of 4, 6 and 8). Over the duration of the trial, there is greater potential that those with syndesmosis screw(s) may require further surgery. To mitigate against risk of allocation imbalance, stratification of this sub-group will be designed into the randomisation.

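### Metalwork removal after randomisation is a candidate covariate in the exploratory models and is blurred with the true stratification factor, syndesmosis screw present at randomisation

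*Protocol article*

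**What the plan says.** The covariate text is in the protocol article under Data processing, after the description of the primary test. Candidate covariates are screened by p value, and those that pass "will be taken forward into a statistical model". A further, optional list follows: "Other exploratory analysis for potential covariates may include impact of smoking, previous level of physical activity", then fracture type, and then "complexity of surgical repair and any subsequent removal of metal work; most notably removal of syndesmosis screw(s) for which stratification was applied at randomisation".

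Allocation and Blinding describes the stratification differently. It explains that over the trial "there is greater potential that those with syndesmosis screw(s) may require further surgery", and that to guard against imbalance "stratification of this sub-group will be designed into the randomisation". The sub-group is therefore the patients who have such screws.

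The timing is given in Participant timeline. "Only after all baseline outcome measures are recorded, does randomisation take place", baseline being the 2-week review. Data are then collected at 6, 12 and 24 weeks, and "at 52 weeks as a long-term follow-up and the trial end point".

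The primary analysis is an unadjusted independent t test on OMAS at 12 weeks. A separate analysis of covariance adjusts OMAS, EQ-5D-5L and A-FORM for their baseline scores. Secondary analyses are described as hypothesis-generating.

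**The concern.** Every other item on the list (smoking, earlier activity, fracture type, complexity of repair) is fixed before allocation. Subsequent removal of metalwork is not, and the plan does not set it apart. Between weeks 2 and 6 the EMADE arm has progressive exercise, manual therapy and weekly contact with a physiotherapist, so an effect of allocation on later removal is possible, though the documents do not claim one. Removal also has no time window. A model of 12-week OMAS could include removals after week 12, some of them perhaps prompted by a poor ankle at week 12. That would be conditioning on a consequence of the outcome.

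Once such a variable is in the model, the arm coefficient is no longer the total effect of being allocated to EMADE. Nor need it be a clean direct effect, because removal and OMAS may share unmeasured causes. If the screening rule is meant to keep variables associated with outcome, a marker of poor recovery is a likely one to be kept.

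The wording adds a second problem. An analyst who wants to adjust for the stratification factor could take this sentence as the instruction and enter removal where screw presence is meant.

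**Working it through.** **1. The plan's own scale.** This point disputes no stated figure, but OMAS shifts need a yardstick. With a difference of 10 and SD 19.5 (Sample size calculations), two-sided 5% and 80% power: n per arm = 2 × (1.96 + 0.84)² × 19.5² / 10² ≈ 59.7, so 60 per arm and 120 in total. The stated 120 reproduces. (Sidedness is not stated; two-sided gives the figure.)

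**2. Timing.** Randomisation follows the baseline measures at the 2-week review, and further surgery is expected over the course of the trial, to 52 weeks. Removal of metalwork is therefore a later event and cannot have been a stratum. Screw presence is known at randomisation and can.

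**3. Size of a possible shift.** The documents give no screw prevalence, removal rate or effect of removal on OMAS. All of the following are assumptions: direct effect of EMADE 10 points; SD 19.5; a proportion π of 10% to 30% with a screw; removal only among those patients, at 20% in one arm and 50% in the other, in either direction; removal changes OMAS by β = −10 or −20.

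- Total effect = 10 + β × π × (p_EMADE − p_usual).
- Adjusted for removal, with no shared causes = 10.
- Shift = |β| × π × |p_EMADE − p_usual|.
- Smallest: 10 × 0.10 × 0.30 = 0.3. Largest: 20 × 0.30 × 0.30 = 1.8.

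A simulation of 1,000,000 records per scenario, analysed by least squares, agrees (simulation error about 2 × 19.5 / √1,000,000 = 0.04). Selected scenarios:

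| π | Removal, EMADE v usual | β | Formula, total | Unadjusted | + screw presence | + screw presence and removal |
|---|---|---|---|---|---|---|
| 10% | 20% v 50% | −10 | 10.3 | 10.27 | 10.27 | 9.96 |
| 10% | 50% v 20% | −10 | 9.7 | 9.71 | 9.71 | 10.01 |
| 20% | 20% v 50% | −20 | 11.2 | 11.25 | 11.24 | 10.07 |
| 20% | 50% v 20% | −20 | 8.8 | 8.85 | 8.86 | 10.06 |
| 30% | 20% v 50% | −20 | 11.8 | 11.81 | 11.81 | 9.99 |
| 30% | 50% v 20% | −20 | 8.2 | 8.27 | 8.27 | 10.06 |
| 30% | 30% v 30% | −20 | 10.0 | 9.96 | 9.96 | 9.96 |

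Adjusting for screw presence leaves the arm difference where it was. Adding removal moves it, up or down according to which arm has more removals.

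**4. Shared causes.** Add an unmeasured recovery factor worth 10 OMAS points per SD that also lowers the log odds of removal by 1 per SD (β = −10; the 20% and 50% now apply at the factor's mean). Adding removal to the model moved the estimate as follows:

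- π = 20%: 10.52 to 9.59, or 9.48 to 10.42.
- π = 30%: 10.83 to 9.43, or 9.21 to 10.62.

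The shifts are 0.9 to 1.4 points, and the adjusted values (9.4 to 10.6) miss the direct effect of 10 as well. With equal removal rates the same factor gave 9.97 to 9.96 and 10.00 to 9.98. In these scenarios it is a difference in removal between arms that causes the shift; shared causes then change its size and meaning.

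**The case against.** The strongest reply is that nothing confirmatory is at risk. The 12-week t test is unadjusted, the baseline-score ANCOVA does not use this variable, and the list is optional and exploratory. The purpose may also be to learn how these factors relate to outcome, not to re-estimate the arm difference. All of this stands and limits the point. It does not dispose of it: the same paragraph sends selected covariates into a model, does not say how the arm coefficient will be presented, and compares adjusted with unadjusted scores for the baseline adjustment.

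Four stronger readings are tempting, and the documents support none of them.

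- *Removal was used as the stratum.* The clause about stratification can attach to the screws rather than to their removal, and Allocation and Blinding settles it: the sub-group is patients with screws. The fault is unclear wording.
- *The true stratum will be left out of the model.* The list is open, no final model is given, and complexity of repair might capture it. Screw presence is not named as a term, but nothing excludes it.
- *Adjustment could remove the treatment effect.* The assumed ranges give a distortion of under 2 points on an effect of 10.
- *The shift could reach 3 points.* That would need, for example, removal to differ by 15 percentage points across the whole arm with a 20-point effect (0.15 × 20 = 3). The ranges above imply whole-arm differences of 3 to 9 percentage points (0.10 × 0.30 to 0.30 × 0.30), and even these rest on a strong contrast among screw carriers.

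It is also fair that the documents do not say how many removals would precede week 12, so the figures may apply less to the 12-week outcome than to later ones.

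**Conclusion.** The point holds as a minor to moderate fault in the exploratory analysis. A post-randomisation event is offered as an adjustment covariate, and the sentence does not keep it apart from the factor used in the randomisation. The timing is certain from the documents. The consequence is conditional: removal must differ by arm, whether through the treatment itself or because a worse outcome leads to removal.

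The size is unknown. Under the assumed ranges it is about 0.3 to 1.8 OMAS points in either direction, or 3% to 18% of the 10-point difference. The upper figure is about half the standard error of the arm difference at 60 per arm (19.5 × √(2/60) = 3.56; 1.8 / 3.56 ≈ 0.5). With equal removal rates there is no material shift. The primary result and the sample size do not change.

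**What to change.** In the covariate paragraph under Data processing, delete subsequent metalwork removal from the variables used to adjust the comparison between arms. Name the randomisation stratum instead: syndesmosis screw present at randomisation, yes or no. State that removal will be reported descriptively by arm. If its relation to outcome is of interest, present that analysis separately, labelled as exploratory and not as an adjusted treatment effect.

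The cost is a sentence or two. The stratum should already be in the randomisation record, and no change to sample size, primary analysis or patient care is involved.

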#### Exclusion criteria

Inability to provide informed consent, or declining participationComorbidities: diabetes requiring prescription drugs, non-healing leg/foot ulcers, oral or intravenously administered steroid users, pre-existing ankle arthritis and concurrent or history of significant ipsilateral or contralateral lower limb injury/condition, e.g. prosthesis in lower-limb joints, or neurological disordersAt the 2-week clinic visit a patient may be excluded if, based on individual clinical decision, there is notable risk that early wound movement will impede satisfactory healing.Those unable to commit to weekly clinic visits, if assigned to the EMADE intervention group

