### Interventions

Pre-operatively and, during the first two post-operative weeks, participants receive identical care consisting of admission to hospital and consultant supervised surgery including management on a standard care pathway. Participants are discharged home in a cast and reviewed 2 weeks following surgery. All participants undergo x-ray post surgery and wound inspection following cast removal during the 2-week review (10 to 19 days post surgery). All participants are non-weight-bearing throughout the study until the 6-week point.

The EMADE intervention is a progressive home exercise programme that includes range-of-motion (ROM) and strengthening exercises, and is conducted by the participant up to six times a day. To be able to conduct the exercises, at the 2-week fracture clinic review, those in the EMADE intervention group are fitted with a removable below-knee cast with Velcro retaining straps.

The EMADE programme starts with light intensity and low daily repetitions, and as the weeks progress, becomes progressively more intensive and repetitive. For example, exercises start resistance-free, and are followed by elastic-exercise-band resistance; while the daily repetitions start twice daily and build up to six times daily. These progressions are taught during weekly face-to-face sessions between the week-2 and week-6 fracture clinic reviews.

During the physiotherapy sessions, participants receive manual therapy consisting of 5 to 10 min of joint and soft-tissue manipulation to the ankle complex. Advice and education is on-going and includes; healing processes, control of pain and swelling, and expectations of fluctuation of pain and swelling. These sessions take part in the recruiting hospital, and are provided by an experienced physiotherapist trained in the application of the EMADE intervention.

To encourage compliance with the EMADE home exercise programme, participants are provided with written and pictorial exercise sheets. These were developed through patient input and include diary sheets, although completion of the diary sheets is neither mandatory nor used in data collection. Participants are not paid to attend, but a basic travel allowance is offered to attend the additional sessions for the study, but not for usual NHS care. Participants in the usual care group are treated in a below-knee cast and remain non-weight-bearing until the 6-week point.

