From the 6-week review, all study participants receive the same standard care. This includes removal of cast and, if appropriate following x-ray, weight-bearing as tolerated may commence, along with physiotherapy as required. Protocol deviations will be as per standard care, being based on individual clinical decisions.

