### Data processing

PROM data collection is paper based, with participant number 55 onwards being offered the option of completing PROMs online. Once paper-based 12-week, 24-week and 52-week PROMs are completed the participant seals them in a windowless opaque envelop and returns them to the researchers (postage pre-paid). These are securely stored and subsequently opened in batches by an individual blinded to group allocation, who inputs the data into a holding database for subsequent transfer into SPSS for reporting and statistical analysis. For audit purpose, after inputting each batch, a ‘read-only’ copy is stored in a separate protected folder. A separate copy is used for data screening and cleaning, guided by good practice [33] and may include self-evident corrections [34] where appropriate. While filters and error alerts will reduce inputting errors, 20% of entries will be cross-checked against the paper PROMs for discrepancies. Data changes will be recorded for blinded adjudication. For audit purposes a copy of the cleaned and checked data will also be saved as a ‘read-only’ copy and stored separately. The design of the e-PROMs does not permit questions to be left unanswered, mitigating against problems of incomplete data and once the participant completes their PROM the original dataset is locked against further alterations. The system permits data transfer into SPSS.

The research team and statistician will conduct the analysis. The statistician will conduct the primary outcome analysis independently and is blinded to group allocation. Data and reason for any patient excluded prior to randomisation will be reported, but not carried into the main analysis. Descriptive statistics will be produced, within and between each intervention group(s) for demographics and outcomes at all data time points. Continuous data will be summarised as mean and standard deviation and confidence intervals (CI) (95% CI and *p* value threshold ≤ 0.05) for the PROM outcome data. Median and interquartile ranges will be used where appropriate statistical assumptions are not met, whereas categorical data will be presented as frequencies and proportions and analysed using either chi-square or Fisher’s exact test as indicated (*p* value of ≤ 0.05). Non-parametric tests will be employed where appropriate. Analysis will be conducted on the intention-to-treat (ITT) basis.

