## Discussion

The aim of this trial is to determine if EMADE is more effective than usual care in reducing symptoms and restoring function in those who have undergone open reduction and internal fixation following a Weber B ankle fracture. While EMADE does not contain novel modalities, what is distinctive for this trial is EMADE’s early clinical application of a progressive ankle rehabilitation programme, being at 2 weeks post ankle surgery versus the traditional of starting after 6 weeks of immobilisation.

We do not anticipate significant bias from known confounders, such as age and sex, and unknown confounders, due to the limiting effect on bias from random allocation. However, as a pragmatic study, there is no control nor influence over the quality and volume of care, including physiotherapy, after the end of the intervention at 6 weeks post surgery.

While compliance with the EMADE home exercise programme will be encouraged through the weekly face-to-face reviews and the written and pictorial exercise sheets, compliance will still be a potential confounder. However, as a pragmatic trial, this level of encouragement and supervision was felt to be appropriate, as it reflects current physiotherapy clinical practice.

It may be argued that starting physiotherapy early with EMADE will reduce the number of sessions subsequently required and, thus, the overall number of sessions may not be significantly different from usual care. However, while this remains unproven it is pertinent to assume that EMADE is more expensive (approximately £54 to £75) and, therefore a cost-utility analysis in QALYs is required from the commissioner’s perspective to determine if EMADE is value for money. Also, while QALY units will be valued by commissioners, the use of natural units; return to driving and return to work will be tangible to patients and their families.

As this intervention requires no specialist equipment, it is suitable for provision in both primary and secondary care-based physiotherapy departments and, therefore, has potential for broad clinical impact. The trial design limits bias where possible, including during the collection, processing and analysis of PROM data. Objective outcomes will be recorded unblinded; however, being secondary outcomes and analysed separately from the PROM data, the potential impact of bias from objective data will have limited impact on the overall quality of the study.

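### The 'modified ITT' analysis excludes participants by EMADE session attendance, so it is a one-arm per-protocol comparison that does not preserve randomisation

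*Protocol article*

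**What the plan says.** The main analysis set is clear: "Analysis will be conducted on the intention-to-treat (ITT) basis" (protocol article, Data processing). Later in the same section, among the baseline-adjusted and covariate analyses, a further analysis is added: "Analysis will also be conducted using modified ITT by excluding those participants who attend only one session or less of EMADE sessions". No arm is named and there is no matching rule for usual care.

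The Interventions section shows who can attend. For EMADE, "These progressions are taught during weekly face-to-face sessions between the week-2 and week-6 fracture clinic reviews". For controls, "Participants in the usual care group are treated in a below-knee cast and remain non-weight-bearing until the 6-week point". Under Participant timeline, randomisation follows the baseline measures taken at 2 weeks, so attendance is observed only after allocation.

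Two statements limit the weight of the point. Data processing says "Secondary analyses will be performed for hypothesis generation". The exclusion criteria list, before randomisation, "Those unable to commit to weekly clinic visits, if assigned to the EMADE intervention group".

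**The concern.** An ITT analysis, including a modified one, is expected to keep the randomised comparison essentially intact. This rule selects on behaviour after randomisation, in one arm only. Participants who stop coming may differ in motivation, pain or complications. Their counterparts in usual care cannot be identified and stay in.

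Complications show how this could matter. Wound risk is judged at the 2-week visit, before randomisation. An EMADE participant who stops attending because of a later wound problem could be dropped, while a control with the same problem is kept. The Background itself raises wound infection as a concern with very early rehabilitation, so the analysis could hide something that the trial needs to see.

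The label adds to the problem. A reader who sees a modified ITT result beside the ITT result may take it as confirmation with the same protection against bias.

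**Working it through.** **Design figure first.** Inputs from Sample size calculations: difference 10, SD 19.5, 5% significance, 80% power. Allocation is 1:1 (Trial design). Sidedness is not stated; two-sided is assumed.

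n per arm = 2 × (1.960 + 0.842)² × 19.5² / 10² = 59.7, so 60 per arm and 120 in total. This reproduces the stated 120.

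**Literal reading.** Usual-care participants attend 0 EMADE sessions, and 0 is within the exclusion rule. Of 60 controls, none remain and there is nothing to compare.

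**Evident reading (EMADE arm only).** Let f be the share of the EMADE arm excluded, and g the mean OMAS of those retained minus that of those excluded. Then:

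retained mean − full-arm mean = f × g

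The documents give neither f nor g; the values below are assumptions. For the error rate, take no treatment effect, 60 per arm before exclusion, an overall SD of 19.5 in each arm and a normal approximation:

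- variance among the retained = 19.5² − f(1 − f)g²
- SE = √[variance among the retained / (60(1 − f)) + 19.5² / 60]
- chance of falsely favouring EMADE = 1 − Φ(1.96 − f × g / SE)

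For f = 20% and g = 10, the retained variance is 380.25 − 16 = 364.25. SE = √(364.25/48 + 380.25/60) = 3.73. The shift is 2.0 and the chance is 1 − Φ(1.96 − 0.54) = 7.7%.

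| f | g | Shift (points) | Falsely favours EMADE (nominal 2.5%) |
|---|---|---|---|
| 5% | 10 | +0.5 | 3.4% |
| 10% | 10 | +1.0 | 4.6% |
| 20% | 10 | +2.0 | 7.7% |
| 20% | 0 | 0 | 2.5% |
| 20% | −10 | −2.0 | 0.6% |

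**Which sessions count.** Health economics prices a session at £18 to £25, and the Discussion puts the extra cost of EMADE at about £54 to £75. 54/18 = 3 and 75/25 = 3, so three additional sessions are implied. The text with Fig. 2 says that the 2-week and 6-week EMADE sessions are combined with the orthopaedic reviews. The threshold may therefore apply to three sessions or to five. If the combined sessions count, anyone who attends both reviews already has two and cannot be excluded. If they do not, someone who attends both reviews and one of the three extra sessions is excluded. The size of f depends heavily on this, and the rule does not say.

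**The case against.** The strongest reply is that little rests on this analysis. It is additional to the ITT analysis, and the protocol calls secondary analyses hypothesis-generating. No sensible analyst would drop every control, and the exclusion rule is printed beside its label, so nothing is concealed. All of this stands and limits the importance of the point. It does not make the comparison a randomised one or the label apt.

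Several stronger readings are tempting but unsupported:

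- **That the analysis must favour EMADE.** The sign follows g, which the documents do not give. If low attenders do as well as the others, the shift is zero. If they stopped because they were well, it reverses.
- **That the bias is large.** The commitment criterion screens out some non-attenders before randomisation. If the combined sessions count, few would be excluded. Some low attenders may also lack 12-week data and be absent from a complete-case analysis anyway. A shift of 2.0 points is below one standard error of the planned comparison, 19.5 × √(2/60) = 3.6.
- **That the protocol admits the confounding.** The Discussion says "compliance will still be a potential confounder", but about the home exercise programme, not session attendance.

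A further fair objection concerns the usual remedy. EMADE participants receive a removable cast at the 2-week review and exercise at home, so those with one session or none may be partly treated. A complier-average analysis with a two-session threshold assumes that allocation does nothing for them. This has to be stated and tested as far as possible; it does not rule the method out.

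**Conclusion.** The point holds as a defect in a stated supplementary rule. The analysis selects on a post-randomisation event in one arm, is mislabelled, and as worded would leave no control arm. This does not depend on any assumed number.

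Bias towards EMADE is plausible but not established. The 0.5–2.0 points rest on an assumed 5–20% excluded and an assumed 10-point deficit, and are 5–20% of the 10-point minimal important difference. The primary ITT result is untouched. The change is worth making because it is cheap and removes a result that could be misread as support for the primary analysis.

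**What to change.** **Wording.** State that the exclusion applies to the EMADE arm only. Label the analysis per-protocol, exploratory and not randomisation-based. Define which sessions count, in particular the week-2 and week-6 sessions combined with the clinic reviews.

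**Adherence question.** Use a complier-average causal effect analysis that keeps all randomised participants: two-stage least squares with allocation as the instrument, session receipt as the exposure, and adjustment for baseline OMAS and the syndesmosis stratum. State the exclusion restriction. Report results for receipt defined as any session and as two or more, because people with few sessions may be partly treated.

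**Cost.** A paragraph of text and one additional model, best settled before outcome data are seen; recruitment was still open when the article was submitted. The article does not say that attendance is recorded, but the rule presupposes it.

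**Downsides.** The interval is wider. Without covariates, the estimate and its standard error are the ITT values divided by 1 − f, so at f = 20% the standard error goes from 3.56 to 3.56/0.80 = 4.45. The exclusion restriction cannot be fully tested. If participants below the threshold gain b points from allocation, the estimate is too high by f × b/(1 − f); for an assumed f = 20% and b = 5, that is 0.2 × 5/0.8 = 1.25 points. The two thresholds should therefore be shown side by side.
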